## I.6. Expected benefits

In the event that this study confirms that the safety and efficacy profile of stereotactic radiotherapy of the operating bed in localized cancers of the oral cavity and oropharynx with risk margins is similar to that of other radiotherapy techniques (brachytherapy or IMRT), stereotactic radiotherapy could become the third therapeutic option to treat localized cancers of the oral cavity and oropharynx with margin at risk.

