### IX.1. Number of topics to include

881 To determine the number of patients needed, two objectives were considered: severe late toxicity at  
882 2 years (primary outcome) and local control rate at 2 years (secondary outcome). The experimental  
883 design follows a one-step Fleming design with no intermediate analysis due to the primary endpoint  
884 which will be evaluated at 2 years (severe late toxicity).

885 The safety and efficacy profile of hypofractionated stereotactic radiotherapy of the operative bed is  
886 expected to be equivalent to other radiotherapy techniques (brachytherapy or normofractionated  
887 IMRT) (cf 3. Rationale of the study for details). In brachytherapy, the rate of late soft tissue ulceration  
888 is around 10-20% and the rate of bone necrosis is around 5-10%. We have decided: 1/ to accept a rate  
889 of less than 5% and 2/ to reject a rate of more than 15%. With a unilateral test for significance ( $\alpha=0.05$ )  
890 with a power of 90% ( $\beta=0.10$ ), the minimum number of patients to be included is 67.  
891 Hypofractionated stereotactic radiotherapy of the operative bed will then be considered an  
892 unacceptable treatment if 6/67 patients (9%) or more have severe late toxicity (grade  $\geq 3$ ).

893 The local control rate of hypofractionated stereotactic radiotherapy is expected to be equivalent to  
894 other radiotherapy techniques (brachytherapy or normofractionated IMRT). We have decided: (i) to  
895 accept a rate of more than 90% and (ii) to reject a rate of less than 80%. With a one-sided significance  
896 test ( $\alpha=0.05$ ) with a power of 80% ( $\beta=0.20$ ), the minimum number of patients to be included is 83.  
897 A lower potency was decided for control as a secondary outcome. Hypofractionated stereotactic  
898 radiotherapy of the operative bed will then be considered an acceptable treatment if 72/83 patients  
899 (87%) or more are locally controlled at 2 years.

900 As a result of these results, and to compensate for possible loss to follow-up, a total of 90 patients  
901 will be included in this study.

902 As the primary objective of this study is estimated at 2 years, once 30 patients have been included  
903 (33% of inclusions), a review of all grade  $\geq 3$  toxicities will be communicated to the independent trial  
904 monitoring committee (IDSMC = *Independent Data and Safety Monitoring Committee*). The grade 4  

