### 933 **IX.3. Main analysis**

934 The analysis of the main objective, i.e. the rate of severe toxicity of grade  $\geq 3$  to 2 years, with its 95%  
 935 CI will be compared to 15% (with regard to the assumptions set in the context of the estimation of  
 936 the number of subjects needed). If the 95% CI does not include this rate, the trial will be considered  
 937 positive. For efficacy endpoints, 95% bilateral confidence intervals will be provided. Statistical  
 938 analysis will be performed on an intention-to-treat basis.

939 An analysis of the predictive factors of severe toxicity of grade  $\geq 3$  to 2 years will be performed. A  
 940 univariate analysis will be performed using the usual tests: Student's test or Mann-Whitney test if the  
 941 conditions of the t-test are not met (normality, and homoscedasticity studied by the Fisher-Snedecor  
 942 test) for quantitative variables and Chi2 test or Fisher's exact test for categorical variables. The  
 943 multivariate analysis will consider a logistic regression model for binary dependent variable.  
 944 Covariates will be retained based on the results of univariate analysis and their clinical relevance.

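### IX.1 ranks toxicity first, but its local-control rule still declares the treatment acceptable without requiring the toxicity criterion, and its toxicity rule is not reconciled with IX.3

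*Protocol*

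**What the plan says.** Protocol IX.1 sizes the trial on two endpoints and ranks them: "2 years (primary outcome) and local control rate at 2 years (secondary outcome"). Local control is given lower power expressly because it is secondary. The design is single-arm, one-step Fleming, without interim analysis.

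For toxicity the plan is to accept a rate "of less than 5% and 2/ to reject a rate of more than 15"%, one-sided alpha 0.05, power 90%, N = 67. The treatment is then called an "unacceptable treatment if 6/67 patients (9%) or more have severe late toxicity".

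For local control the plan is to accept more than 90% and reject less than 80%, one-sided alpha 0.05, power 80%, N = 83. The closing sentence reads "radiotherapy of the operative bed will then be considered an acceptable treatment if 72/83 patients" or more are locally controlled at 2 years.

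IX.3 gives the only rule at trial level, on toxicity alone. The grade 3 or higher rate is compared with 15%: "If the 95% CI does not include this rate, the trial will be considered" positive. I.6, in the rationale, describes what could follow if the study confirms the safety and efficacy profile.

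**The concern.** The two sentences in IX.1 have the same grammatical subject, the treatment, and give opposite kinds of verdict on it. Neither refers to the other. The second is worded as a verdict on the treatment and is triggered by the secondary endpoint alone. Nothing says what is concluded when both criteria are met by the same data.

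IX.3 does not settle this. It defines when the trial is positive, not when the treatment is acceptable, and it uses a different toxicity criterion from IX.1. A toxicity count can therefore escape the unacceptable verdict in IX.1 and still fail to make the trial positive in IX.3.

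At stake is a report that could cite a written protocol criterion for calling the treatment acceptable when the primary safety criterion has failed.

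**Working it through.** **Inputs (all from IX.1 and IX.3).** Toxicity 5% versus 15%, unacceptable at 6/67 or more. Local control 90% versus 80%, acceptable at 72/83 or more. Trial positive if the 95% CI for toxicity excludes 15%, read here as lying wholly below 15%. The correlation between the endpoints is not given, so independence is assumed and bounds over any dependence are shown.

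**The plan's own sample sizes.** n = [(z_α√(p0q0) + z_β√(p1q1)) / (p1 − p0)]².
- Toxicity, p0 = 0.05, p1 = 0.15: [(1.645 × 0.2179 + 1.282 × 0.3571) / 0.10]² = 66.6, so 67.
- Local control, p0 = 0.80, p1 = 0.90: [(1.645 × 0.4 + 0.842 × 0.3) / 0.10]² = 82.9, so 83.

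Both reproduce.

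**Exact binomial behaviour of each written rule.**

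| Rule | True rate | Probability |
|---|---|---|
| Unacceptable, ≥ 6/67 | 15% | 0.949 |
| Unacceptable, ≥ 6/67 | 5% | 1 − 0.882 = 0.118 |
| Acceptable, ≥ 72/83 | 90% | 0.877 |
| Acceptable, ≥ 72/83 | 80% | 0.076 |

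**Both verdicts in one trial.**
- At 15% toxicity and 90% control: 0.949 × 0.877 = 0.83. Bounds: 0.949 + 0.877 − 1 = 0.826, up to 0.877.
- At the design target, 5% and 90%: 0.118 × 0.877 = 0.103. Bounds: 0 to 0.118.

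**If the toxicity criterion had to be met as well.** At 15% toxicity and 90% control the chance of calling the treatment acceptable falls from 0.877 to 0.051 × 0.877 = 0.045, and cannot exceed 0.051.

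**IX.1 against IX.3 at 67 patients.**
- 4/67: Clopper-Pearson 95% upper limit 14.6%. Not unacceptable, and positive.
- 5/67 (7.5%): upper limit 16.6%. Not unacceptable, and not positive.
- 6/67 (9.0%): unacceptable.

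So 5/67 falls between the rules. IX.3 does not name the interval method. Wilson also keeps 15% inside at 5/67. A simple Wald interval would not: 0.0746 + 1.96 × √(0.0746 × 0.9254 / 67) = 0.138. Whether the sections agree thus depends on a choice the text does not make.

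The two criteria also differ in power at 5% toxicity: 0.882 for ≤ 5/67 and 0.757 for ≤ 4/67, against the 90% stated.

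**Joint power, only if both endpoints are required.** With the written cut-offs (≤ 5/67 and ≥ 72/83): 0.882 × 0.877 = 0.773. Bounds: 0.882 + 0.877 − 1 = 0.759, up to 0.877. Multiplying the nominal powers, 0.90 × 0.80 = 0.72, does not describe these cut-offs.

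**The case against.** The strongest reply is that the plan does have a hierarchy. Toxicity is labelled primary throughout, local control is given less power because it is secondary, and trial success in IX.3 rests on toxicity alone. With a Clopper-Pearson interval, a treatment at 15% toxicity would make the trial positive in only 2.0%, 1.0% or 1.3% of trials at n = 67, 83 or 90. The 72/83 sentence closes a paragraph on local control, in a visibly translated text, and can be read as acceptable in that respect only. An analysis plan, not shown, may settle the interpretation.

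Much of this stands, and it rules out stronger readings. A reader might infer that the endpoints are unranked; IX.1 says otherwise. A reader might also infer several alternative routes to success, each at full alpha, and hence a false-positive rate of about twice 5%. No passage says that meeting either rule is enough, and the favourable side of a 95% interval carries about 2.5%, not 5%. Nor does I.6 make both endpoints mandatory: it is rationale, not a decision rule.

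What does not stand is that the ranking cures the wording. Calling an endpoint secondary does not cancel a written criterion that declares the treatment acceptable. Nor is this something properly left to an analysis plan: the protocol itself fixes both rules, and an analysis plan cannot follow both when they disagree.

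**Conclusion.** The point holds as a defect in the decision rules. IX.1 ranks the endpoints, but its favourable verdict on the treatment is not conditioned on the primary one. Taken literally, the two verdicts contradict each other in about 83% of trials at 15% toxicity and 90% control (82.6% to 87.7% over any dependence), and in about 10% at the design target (0 to 11.8%). These figures rest on exact binomials and the denominators of 67 and 83 written in IX.1.

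Separately, IX.1 and IX.3 do not use the same toxicity criterion. With a Clopper-Pearson or Wilson interval they part at 5/67; with a Wald interval they would not.

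The documents do not support a claim of inflated type I error for the trial's own success rule. A shortfall in joint power arises only if the sponsor chooses to require both endpoints.

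**What to change.** 1. In IX.1, reword the 72/83 sentence so that it concerns the endpoint, for example: local control will be considered sufficient if 72/83 or more patients are controlled at 2 years.
2. In IX.1 and IX.3, state that no favourable verdict on the treatment can be given unless the primary toxicity criterion is met.
3. Use one toxicity criterion in both sections: either the count or the interval, with the interval method named. Report its alpha and power.
4. State the role of local control. If it is supportive only, no joint power is needed. If both endpoints are required for the treatment to be acceptable, report the joint power of the cut-offs used: about 77% for ≤ 5/67 with ≥ 72/83 under independence, or 0.757 × 0.877 = 0.66 if the toxicity criterion becomes ≤ 4/67.

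The cost is a few sentences of protocol wording, carried into the analysis plan, and no additional patients. The one real consequence is that the power quoted for the overall conclusion may be lower than the 90% and 80% now shown.

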## STATISTICAL CONSIDERATIONS

### Estimating the number of patients needed

With a one-step Fleming plan, the calculation of the number of patients needed takes into account:

- The primary endpoint: severe toxicity at 2 years limited to 5-15%, minimum N is equal to 67 patients (unilateral,  $\alpha = 0.05$ ,  $\beta=0.10$ )
- and the secondary endpoint: 2-year local control of 80-90%, minimum N is equal to 83 patients (unilateral,  $\alpha = 0.05$ ,  $\beta=0.20$ )

In order to compensate for possible loss to follow-up, 90 patients will be included.

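### The local-control rule of 72/83 has an exact one-sided type I error of 7.6%, not the stated 5%; the cut-off that fits N = 83 is 73/83, with power of about 79.5%

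*Protocol*

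**What the plan says.** Section IX.1 of the Protocol considers two objectives: severe late toxicity at 2 years (primary) and local control at 2 years (secondary). The "design follows a one-step Fleming design with no intermediate analysis due to the primary endpoint".

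For local control the stated inputs are:

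- **Rates:** "accept a rate of more than 90% and (ii) to reject a rate of less than 80"%.
- **Sidedness and error rates:** "With a one-sided significance" "test ( $\alpha=0.05$ ) with a power of 80"%.
- **Sample size:** "the minimum number of patients to be included is 83". The synopsis repeats the 80–90% range, one-sided alpha 0.05 and beta 0.20, and says "minimum N is equal to 83 patients". It gives no cut-off.
- **Decision rule (section IX.1 only):** the treatment "will then be considered an acceptable treatment if 72/83 patients" ("87%) or more are locally controlled at 2 years").

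Enrolment is set at 90 to allow for loss to follow-up.

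**The concern.** In a one-stage design, the hypotheses, alpha and N together fix the cut-off. Here the cut-off is one patient lower than those inputs allow. A treatment whose true local control is exactly the rate the Protocol sets out to reject would be called acceptable more often than the stated 5%. The trial has one arm, so there is no control group against which a lenient threshold would show up. This count is also the only criterion in the Protocol by which local control is judged acceptable or not.

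The wording does not leave room for reading the rule as more than 72. The text says 72 or more, and the printed 87% matches 72/83 = 86.7%, whereas 73/83 = 88.0%.

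**Working it through.** **Inputs** (section IX.1; rates, N and error rates also in the synopsis): p0 = 0.80, p1 = 0.90, one-sided alpha = 0.05 (z = 1.645), power = 0.80 (z = 0.8416), N = 83, success if X ≥ 72.

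**Step 1. Reproduce N.** One-sample normal formula:

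n = [(1.645·√(0.80·0.20) + 0.8416·√(0.90·0.10)) / (0.90 − 0.80)]² = [(1.645·0.4 + 0.8416·0.3) / 0.1]² = 82.9, rounded up to 83.

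This is the Protocol's figure, so the inputs have been read as intended.

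**Step 2. Fleming boundary for N = 83.**

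N·p0 + 1.645·√(N·p0·(1 − p0)) = 66.4 + 1.645·√13.28 = 66.4 + 1.645·3.644 = 72.39.

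The first whole count above this is 73.

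**Step 3. Exact binomial operating characteristics at N = 83.** Alpha is P(X ≥ r | 83, 0.80); power is P(X ≥ r | 83, 0.90).

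| Cut-off r | r/83 | Exact alpha | Exact power |
|---|---|---|---|
| 71 | 85.5% | 0.128 | 0.931 |
| 72 (Protocol) | 86.7% | 0.0760 | 0.877 |
| 73 | 88.0% | 0.0412 | 0.795 |
| 74 | 89.2% | 0.0202 | 0.684 |

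The Protocol's rule runs at 0.0760/0.05 = 1.5 times its stated alpha. No cut-off at N = 83 meets both stated limits exactly: 72 fails on alpha, and 73 misses 80% power by half a point. The smallest design that meets both exactly is 72/82 (alpha 0.046, power 0.806), so a count of 72 belongs with 82 patients.

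**Step 4. Does an approximation explain 72?** With the variance taken at 80%, the normal test for X ≥ 72 gives (72 − 66.4)/3.644 = 1.54, p = 0.062. With continuity correction it gives (71.5 − 66.4)/3.644 = 1.40, p = 0.081. Both exceed 0.05. A Wald test, with the variance at the observed rate, does pass: SE = √(0.8675·0.1325/83) = 0.0372 and (0.8675 − 0.80)/0.0372 = 1.81, p = 0.035. The true error rate of the rule remains 7.6% whichever approximation leads to it.

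**Step 5. The rule expressed as a one-sided 95% lower bound above 80%.**

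| Result | Wald (plain Greenwood, no censoring) | Exact (Clopper-Pearson) | Log-log |
|---|---|---|---|
| 71/83 | 0.792 | | |
| 72/83 | 0.8675 − 1.645·0.0372 = 0.806 | 0.790 | 0.792 |
| 73/83 | | 0.804 | |

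The Wald bound accepts 72/83. The exact and log-log bounds do not.

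**Step 6. Other evaluable numbers.** The smallest count with exact alpha ≤ 0.05 at p = 0.80 is 73 of 83, 77 of 87, 77 of 88, 78 of 89 and 79 of 90. At 79/90 alpha is 0.038 and power 0.814. Carrying 87% over to 90 patients would give 78/90, with alpha 0.069.

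**The case against.** The arithmetic is hard to dispute, but there is a fair case that it matters less than it first appears.

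- **Secondary endpoint.** Section IX.1 deliberately gives local control lower power because it is secondary. Section IX.3 defines a positive trial by toxicity alone (95% confidence interval against 15%) and plans only two-sided 95% intervals for efficacy endpoints, without mentioning the count. Section IX.2 calls the trial exploratory. A reader might infer that the trial's main conclusion is compromised; these sections do not support that. But section IX.1 does call the treatment acceptable on this count, so the rule is not merely descriptive. The exploratory label concerns adjustment for multiple tests and does not excuse a cut-off that misses its own alpha.
- **72 can come from a common approximation.** A Wald test yields it. That may explain the figure, but it does not bring the error rate down to 5%. The Protocol also names a Fleming design, whose boundary gives 73.
- **73/83 is not a perfect match.** Exact power is 79.5%, so it does not deliver everything stated. This stands and should be disclosed. It is a shortfall of half a point, against an excess of 2.6 points on alpha with 72.
- **Ninety patients are enrolled.** A reader might infer that the rule should be 79/90, or that the lack of a cut-off for 90 is an error. The extra patients cover losses, so something near 83 evaluable is what the design expects; 79/90 applies only if all 90 are evaluable. How the rule adapts to the evaluable number is commonly left to the analysis plan, which is not at hand.

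**Conclusion.** The cut-off in section IX.1 is wrong for the design stated there. At 72/83 the exact one-sided type I error is 7.6% instead of 5%, with power 87.7%. At 73/83 it is 4.1%, with power 79.5%. The result assumes 83 evaluable patients, a binary 2-year outcome and the stated 80% and 90% rates. It does not depend on the choice between the exact calculation and the Fleming boundary.

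This should be fixed, though the trial does not hinge on it. N = 83, the enrolment of 90 and the primary toxicity conclusion are unaffected. A reader might also take any one-sided 95% lower bound above 80% as an equivalent rule. It is not: a Wald or plain Greenwood bound would still accept 72/83.

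**What to change.** In section IX.1, replace 72/83 (87%) by 73/83 (88%), and state the exact operating characteristics: one-sided alpha 4.1%, power about 79.5%.

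Add one sentence for the case where the number evaluable differs from 83: use the smallest count whose exact binomial one-sided alpha at 80% is at most 0.05. For example, this is 79/90 (alpha 3.8%, power 81.4%) only if all 90 patients are evaluable. If the rule is instead expressed as a one-sided 95% lower bound above 80%, name the interval as exact (Clopper-Pearson) or, for a Kaplan-Meier estimate, log-log.

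The cost is one figure and a sentence or two, with no extra patients and no design change. Power falls from an unstated 87.7% to 79.5%, close to the planned 80%. The synopsis gives no cut-off and needs no change. The analysis plan was not available; if it repeats the count, it needs the same correction.

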### 906 IX.2. Data analysis: general

907 Patients will be described and compared between groups at baseline according to the following  
908 variables:

- 909 • Compliance with eligibility criteria
- 910 • Epidemiological characteristics
- 911 • Clinical and treatment characteristics.

912 A description of the deviations from the protocol, the patients distributed according to these  
 913 deviations and the causes of abandonment will also be carried out. The number of patients included  
 914 and the curve of inclusions will be presented by groups.

915 Continuous variables will be presented as a mean and standard deviation, subject to the normality of  
 916 their distribution (Shapiro-Wilk test if necessary). In case of non-normality, they will be presented in  
 917 the form of median, quartiles and extreme values. The qualitative variables will be expressed in terms  
 918 of numbers and associated percentages. 95% confidence intervals (95% CI) will be reported. For each  
 919 variable, the number of missing data will be specified. Graphical representations will be associated  
 920 with these analyses as much as possible.

921 The estimate of the theoretical follow-up time will be the time difference between the date of inclusion  
 922 and the date of the database freeze. The follow-up will also be estimated according to the reverse  
 923 Kaplan Meier method for the observed follow-up. The parameters related to the time to events (SSR,  
 924 OS...) as well as the time to deterioration of quality of life (scores) will be estimated according to the  
 925 Kaplan-Meier method and described with a median confidence interval and rates at defined periods.  
 926 Patients without specific events at the time of study termination (baseline freeze of study data) will  
 927 be censored, for the "time to events" criteria, as of the date of the last update. Possible comparisons  
 928 between independent groups will consider the log-rank test (univariate analysis) and the Cox model  
 929 (multivariate analysis).

930 Tests will be bilateral, and a  $p < 0.05$  value will be considered statistically significant. As this trial  
 931 is exploratory, the adjustment of the risk of error of the first kind will not be proposed systematically,  
 932 but on a case-by-case basis in view of clinical and not only statistical considerations (48).

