  - 580 ❖ CT scan or cervicofacial MRI (*The choice between MRI and CT is left to the*
  - 581 *discretion of the investigator but follow-ups must be carried out with the same*
  - 582 *technique*)
  - 583 ❖ Chest CT scan (*The use of PET-FDG is left to the choice of the investigators in each*
  - 584 *center if it is medically indicated*)
- 585 • EORTC QLQ-C30 and H&N35 questionnaire to be completed at **12 months and 24 months,**
- 586 in the absence of local, locoregional or distance progression.
- 587

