### 670 **VI.9. Quality of life assessment**

671 Quality of life (QoL) is assessed by the European *Organisation for Research and Treatment of Cancer*  
672 (*EORTC*) questionnaires QLQ-C30 and QLQ-H&N35, French version.

673 The QLQ-C30 questionnaire (*Appendix 3*) is a cancer-specific questionnaire that consists of 30  
674 questions. Twenty-four questions participate in 9 multi-item scales: 5 functional scales (physical,  
675 role/position, cognitive, emotional, social), 3 symptom scales (fatigue, nausea/vomiting, pain) and  
676 one global condition scale. The remaining six questions are single-item scales assessing symptoms  
677 (dyspnea, insomnia, loss of appetite, constipation, diarrhea) and financial difficulties.

678 The QLQ-H&N35 questionnaire (*Appendix 3*) is a specific questionnaire for patients who have ENT  
679 cancer that consists of 35 questions. Twenty-four questions participate in 7 multi-item scales that  
680 assess ENT pain, swallowing, senses (taste and smell), speech, eating in society, social contacts and  
681 sexuality. The remaining 11 questions are uni-item scales describing specific concerns of patients  
682 with ENT cancer (dentition, mouth opening, dry mouth, sticky saliva, coughing, feeling unwell,  
683 taking painkillers, nutritional supplements, feeding tube, weight loss or gain).

684 The moments of collection of the quality of life questionnaires are:

- 685 • At the inclusion visit, i.e. after informed consent has been obtained and before the start of
- 686 stereotactic radiotherapy
- 687 • At the 30±5-day follow-up visit after stereotactic radiotherapy
- 688 • At the follow-up visit 12 months±10 days after stereotactic radiotherapy
- 689 • At the 24-month follow-up visit±10 days post-radiotherapy

690

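### The Kaplan-Meier median planned for time to quality-of-life deterioration would largely reflect a questionnaire calendar of inclusion, 1, 12 and 24 months; the planned rates remain usable

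*Protocol*

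**What the plan says.** Section IX.2 treats quality-of-life deterioration like recurrence-free and overall survival. These parameters, "as well as the time to deterioration of quality of life (scores) will be estimated according to the" "Kaplan-Meier method and described with a median confidence interval and rates at defined periods". Patients without an event are censored at the date of the last update.

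Section VI.9 gives four collection times:
- "At the inclusion visit, i.e. after informed consent has been obtained and before the start of" radiotherapy;
- "At the 30±5-day follow-up visit after stereotactic radiotherapy";
- "At the follow-up visit 12 months±10 days after stereotactic radiotherapy";
- "At the 24-month follow-up visit±10 days post-radiotherapy".

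Section VI.5 and the flow chart (Table 1) agree. The clinic visits at 3, 6, 9, 15, 18 and 21 months carry no questionnaire. Section VI.5.2 restricts the 12- and 24-month questionnaires to patients seen "in the absence of local, locoregional or distance progression", and Section VI.5.3 limits follow-up after recurrence to vital status.

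Section IX.4 sets 10 points as the smallest clinically relevant difference, with a 5-point sensitivity analysis, and plans a mixed model for change by measurement time.

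**The concern.** A Kaplan-Meier curve takes the recorded date as the event date. Here a deterioration is known only to lie between two questionnaires, and two of the gaps are about a year long. Dated at the visit that reveals it, the event can only be late, and the curve can drop only around questionnaire dates. The median and its confidence limits are read off those steps. A reader would take the result as the typical time to deterioration, when it mainly shows which questionnaire came next.

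The protocol names both the method with its summary and the schedule that cannot support that summary. This is therefore a mismatch within the document, not a detail left for the analysis plan.

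**Working it through.** The protocol gives no figure for time to deterioration, so there is none to reproduce.

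**Delay.** Nominal gaps after radiotherapy are 12 − 1 = 11 months and 24 − 12 = 12 months. These are the largest delays for events inside them. If events were uniform within a gap, the mean delay would be half of it, 5.5 or 6 months. Uniformity is an assumption, and the figures apply only to events in those gaps. Deterioration already present at the 30-day visit falls in a much shorter interval.

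**Where the median can fall.** With events dated at the visits, the estimated median is the first of 1, 12 and 24 months at which the deterioration-free proportion S is 50% or less; otherwise it is not reached. For illustration, take exponential times with an assumed true median m, so S(t) = 0.5^(t/m). For m = 10, S(12) = 0.5^(12/10) = 44%.

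The last column is the typical Kaplan-Meier median over 300 simulated trials of 90 patients. Visits were spread over the protocol windows (±5 days at 1 month, ±10 days later), and patients without deterioration were censored at their last questionnaire.

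| Assumed true median (months) | S(1) | S(12) | S(24) | Median on nominal dates | Simulated, with windows |
|---|---|---|---|---|---|
| 2 | 71% | 2% | 0% | 12 | 11.9 |
| 6 | 89% | 25% | 6% | 12 | 12.1 |
| 10 | 93% | 44% | 19% | 12 | 12.2 |
| 13 | 95% | 53% | 28% | 24 | 23.7 |
| 15 | 95% | 57% | 33% | 24 | 23.9 |
| 20 | 97% | 66% | 44% | 24 | 24.1 |
| 26 | 97% | 73% | 53% | not reached | 24.2 |

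The S(12) and S(24) columns separate scenarios that the median merges. Near a boundary the median is also unstable: with a true median of 11 months, 74% of runs gave about 12 and 26% about 24.

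**Visit windows.** For a true median of 26 months, beyond follow-up, a finite median appeared in 99.7% of runs with actual visit dates, against 32% with nominal dates. Patients still free of deterioration are censored at their own 24-month visit, so later events within the window are divided by a shrinking risk set.

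**Variants.**
- With 25% dropout by 24 months, true medians of 3, 6, 10, 15 and 20 gave 11.9, 12.1, 12.2, 23.8 and 24.0: the same pattern.
- Counting from inclusion moves the clusters by about a month and does not remove them.
- With death as an event, assume 28% dead at two years (100 − 72, from the 72% two-year survival of one brachytherapy series in Section I.2.1). Counted from inclusion, the typical median stayed at 12.4 to 13.2 for true medians of 3 to 15 months, but fell off the grid for longer ones (17.3 for a true median of 20).

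**Censoring.** Read literally, censoring at the last update keeps a relapsed patient at risk after the questionnaires have stopped. That patient can no longer show a deterioration, which lengthens the apparent time.

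**The case against.** The strongest reply is that the usable summary is already planned. Section IX.2 asks for rates as well as a median, and those at 12 and 24 months are the deterioration-free proportions. Section IX.4 already fixes the 10- and 5-point thresholds and plans a mixed model that suits the schedule. Section IV.2 defines the quality-of-life endpoint only by the two questionnaires, and no decision rule uses time to deterioration. Kaplan-Meier also validly estimates time to first documented deterioration, and the dating rule and event definition can wait for the analysis plan. All of this stands. It limits the point to the median and its interval but does not rescue them, because the protocol itself commits to reporting them on this schedule.

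A reader might infer more than the documents support:
- That the whole quality-of-life analysis fails. It does not; the rates and the mixed model remain usable.
- That the bias is about 5.5 to 6 months overall. That needs uniform event times and applies only within the long gaps.
- That the median must always sit on the grid. It may be not reached, and deaths counted as events could move it off.
- That the result could not be compared with other series. The documents give no quality-of-life series to compare it with.

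**Conclusion.** The point holds for the median time to quality-of-life deterioration and its confidence interval, and for nothing wider. If deterioration is dated at the visit where it is first seen and death is not an event, the median lies near 1, 12 or 24 months after radiotherapy or is not reached. Individual dates in the long gaps are up to 11 or 12 months late. The true medians in the table are assumptions, and the actual bias is unknown because the documents give no deterioration rate. The importance is minor: the analysis is secondary and descriptive, and it bears on neither the toxicity nor the local-control decision.

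**What to change.** In Section IX.2, or in the analysis plan:
- Drop the median and its confidence interval for time to quality-of-life deterioration.
- Report the deterioration-free rates already planned (10-point threshold, 5-point sensitivity analysis) at 1, 12 and 24 months with 95% confidence intervals. Assign each questionnaire to its nominal visit time, so that the spread of dates within a window does not distort the curve.
- If a time scale is wanted, use an interval-censored (Turnbull) estimate. It will place the median only within an interval, such as 1 to 12 months, and at the visit times it will say essentially what the rates say.
- Censor quality of life at the last completed questionnaire instead of the last update.
- State that the 12- and 24-month estimates rest on patients without progression, who are a selected group.

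The cost is a change of wording before the database freeze and the loss of a single summary median. No visit or questionnaire is added.
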